Radix paeoniae alba (*bai shao*)	11.8	5	10	TCM: 1. Nourishing blood and constraining *yin*. 2. Emolliating the liver and relieving pain Pharmaceutical study: 1. Analgesic effect. 2. Antimicrobial and anti-inflammatory effect. 3. Immunologic effect
Herba ecliptae (*mo han lian*)	11.8	5	10	TCM: 1. Enriching the *yin* of the kidney and the liver. 2. Cooling the blood and stopping bleeding Pharmaceutical study: 1. Enhancing immunity. 2. Protecting the liver. 3. Antimutagenic activity
Radix bupleuri (*chai hu*)	11.8	5	10	TCM: 1. Releasing the exterior and abating fever. 2. Soothing liver-*qi* stagnation. 3. Increasing *yang qi* Pharmaceutical study: 1. Inhibiting the central nervous system. 2. Anti-inflammatory and antimicrobial effects. 3. Enhancing immunologic function. 4. Protecting the liver
Xanthii fructus (*cang er zi)*	11.8	5	10	TCM: 1. Dispersing wind and cold. 2. Dispelling dampness. 3. Relieving nasal congestion. 4. Relieving pain Pharmaceutical study: 1. Relieving nasal symptoms. 2. Antimicrobial activity. 3. Preventing coughing
Radix et rhizoma glycyrrhizea (*gan cao*)	5.9	2.5	5	TCM: 1. Tonifying the spleen and replenishing *qi*. 2. Dispelling phlegm and suppressing coughing. 3. Relaxing tension and relieving pain. 4. Clearing heat and detoxifying. 5. Harmonizing medications Pharmaceutical study: 1. Protecting the digestive system. 2. Antiallergic and anti-inflammatory effects

If a participant cannot take the medication for any particular reason, a record will be made, and the medicine will be conserved and returned to the researchers at the end of the study. Two follow-up telephone visits will be performed during the treatment period. Participants who complete treatment will be followed up three times over the course of 3 months (Fig. 2). No other treatment for AR will be allowed for any participant in either group during the study period. The rescue medication, desloratadine tablets (5 mg orally every night, Hainan Poly Pharmaceutical Co., Ltd., Chinese State Food and Drug Administration approval number: H20040972), will be provided for participants who may experience AR episodes. Administration of the rescue medication will be recorded and statistically analyzed as an indicator of a curative effect.

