### Outcome measurement

The primary outcome is a change in the Total Nasal Symptom Score (TNSS) [40]. Secondary outcome measures are as follows: (1) changes in the standard version of the Rhinoconjunctivitis Quality of Life Questionnaire (RQLQ(S)) score; (2) the frequency of AR episodes and their severity (visual analog scale, VAS); (3) changes in the serum levels of cytokines IL-4, interferon-γ (IFN-γ), transforming growth factor β-1 (TGF-β1), and interleukin-17 (IL-17), and changes in the gut microbiota composition in stools before and after treatment. In addition, participants will complete a medicine diary and report any AEs related to the intervention drugs throughout the trial.

The TNSS evaluates the following four nasal symptoms: rhinorrhea, nasal obstruction, nasal itching, and sneezing. The symptoms are self-assessed and recorded by subjects using a four-point scale (0 = no symptoms, 1 = mild symptoms, 2 = moderate symptoms, and 3 = severe symptoms), with low scores indicating less severe nasal symptoms [40]. The RQLQ(S) is a disease-specific questionnaire that can assess quality of life impairment in AR patients. This questionnaire consists of 28 questions covering the following seven domains: activities, sleep, non-nose/eye symptoms, practical problems, nasal symptoms, eye symptoms and emotional problems [41]. The RQLQ(S) with standardized activities is an updated version of the original RQLQ [42]. It has been translated into different languages and has frequently been used in different countries. The VAS, which ranges from 0 (nasal symptoms not at all bothersome) to 10 (nasal symptoms extremely bothersome) was designed to assess the severity of nasal symptom disturbance and has been validated for use in the quantitative evaluation of AR severity [43]. The TNSS, RQLQ(S), and frequency and severity of AR episodes will be evaluated at the beginning of, middle of and after the treatment period and at the end of each month during the 3-month follow-up period (Fig. 2).

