### Sample size calculation

This study is mainly focused on determining the efficacy of BMF for AR patients with LSQDS. The primary outcome is the TNSS. With reference to data from a previous study [46] and our clinical observations, the sample size was calculated using the noninferiority test for two means with software PASS 2011. We assumed that the TNSS of the treatment group will be 5.53 ± 2.79 and that of the control group will be 6.64 ± 3.06. To obtain a significance level of 5%, a power of 90%, and a noninferiority margin of 0.92, 74 participants are required. Allowing for an 8% dropout rate, 80 participants are needed, with 40 in each group.

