### Data analysis

All data analyses will be conducted according to the intention-to-treat principle, and the analysis will be performed in a double-blind manner by qualified statisticians. The EpiData 3.1 software will be used to build the database, and missing data will be replaced with the mean or median of the item for the homogeneous participant population according to complete data. Two similar participants with complete data will be subjected to repeated review, and a logic check will be performed to confirm that the data are correct before analysis.

The data will be analyzed using the Statistical Package for the Social Sciences version 17.0 (SPSS 17.0). Measured data will be expressed as the mean, median, minimum, and maximum values. Comparisons between the two groups will be analyzed by analysis of variance and pairwise comparisons (univariate variance will be assessed with the rank-sum test). Count data will be expressed as the composition ratio and the rate. Between-group efficacy will be assessed using the χ^2^ test, and ranked data will be analyzed with the rank-sum test. A baseline comparison test will be performed at a significance level of α = 0.10, and an efficacy analysis will be performed at a significance level of α = 0.05.

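### The Data analysis section names a chi-square test for efficacy, although efficacy is defined by a numeric TNSS and the trial is sized on a noninferiority test of two means

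*Protocol article*

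**What the plan says.** Four places in the protocol article bear on this.

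- **Outcome measurement:** "The primary outcome is a change in the Total Nasal Symptom Score (TNSS"). TNSS sums four nasal symptoms, each scored 0 to 3. The secondary outcomes are RQLQ(S), frequency and VAS severity of AR episodes, four cytokines and gut microbiota. No effective rate, responder definition or TNSS cut-off is given there or elsewhere in the article.
- **Sample size calculation:** "the sample size was calculated using the noninferiority test for two means", with assumed TNSS of 5.53 ± 2.79 (BMF) and 6.64 ± 3.06 (control), 5% significance, 90% power and a margin of 0.92. This gives 74 participants, raised to 80 for dropout.
- **Data analysis:** after describing measured data, the section says "Comparisons between the two groups will be analyzed by analysis of variance and pairwise comparisons". It then says "Count data will be expressed as the composition ratio and the rate", followed directly by "Between-group efficacy will be assessed using the χ^2^ test", and in the same sentence sends ranked data to the rank-sum test. It sets α = 0.05 for the efficacy analysis without saying which test that is, and does not mention noninferiority or the margin.
- **Interventions:** "Administration of the rescue medication will be recorded and statistically analyzed as an indicator of a curative effect". Rescue use is not in the outcome list.

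**The concern.** A chi-square test needs a categorical outcome. The quantity that defines efficacy here is a numeric score, and the number of patients was chosen so that its means could be compared. A statistician who follows the efficacy sentence to the letter must either cut TNSS into response and non-response or pick some other variable, and the article defines no such cut.

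What is at stake is mainly power. Dichotomising a score discards information, and an ordinary chi-square test looks for a difference instead of testing against the margin. A trial sized for the noninferiority comparison of means would be far too small for it.

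**Working it through.** **Inputs (Sample size calculation).** Means 5.53 and 6.64, SDs 2.79 and 3.06, margin 0.92, 74 evaluable participants (37 per arm). A lower TNSS is better.

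**Step 1: reproduce the plan's own figure.**
- Expected difference in favour of BMF: 6.64 − 5.53 = 1.11.
- Distance from the margin: 1.11 + 0.92 = 2.03.
- SD = √[(2.79² + 3.06²)/2] = √[(7.784 + 9.364)/2] = 2.928.
- Standard error at 37 per arm = 2.928 × √(2/37) = 0.681.
- Noncentrality = 2.03/0.681 = 2.98 on 72 degrees of freedom. The one-sided 0.05 critical value is 1.666, and power is 90.5%.

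The smallest t-based size that reaches 90% is 37 per arm, or 74 in total, which matches exactly. One-sided 0.025 would need 45 per arm. The article does not say whether its 5% is one- or two-sided, so one-sided 0.05 is inferred from this match. With 40 per arm the power is 92.3%.

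**Step 2: power of a chi-square test on the same scores.** Count a patient as a responder if TNSS ≤ c and assume normal scores. The response rates are then p₁ = Φ[(c − 5.53)/2.79] and p₂ = Φ[(c − 6.64)/3.06]. With p̄ the average of the two rates:

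power = Φ[(p₁ − p₂ − 1.96·se₀)/se₁], where se₀ = √[2p̄(1 − p̄)/n] and se₁ = √{[p₁(1 − p₁) + p₂(1 − p₂)]/n}

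Example, c = 5 and n = 37: p₁ = 0.425, p₂ = 0.296, se₀ = 0.112, se₁ = 0.111, power = 20.8%.

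| c | BMF rate | Control rate | Power, 37 per arm | Power, 40 per arm | Per arm for 90% power |
|---|---|---|---|---|---|
| 3 | 18.2% | 11.7% | 11.9% | 12.5% | 629 |
| 4 | 29.2% | 19.4% | 16.2% | 17.1% | 404 |
| 5 | 42.5% | 29.6% | 20.8% | 22.1% | 291 |
| 6 | 56.7% | 41.7% | 24.8% | 26.5% | 233 |
| 7 | 70.1% | 54.7% | 27.4% | 29.3% | 206 |
| 8 | 81.2% | 67.2% | 27.8% | 29.7% | 203 |

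Simulating the test itself at 37 per arm (200,000 trials) gives 13% at c = 3, rising to 28% at c = 8. The noninferiority test succeeds in 90% of the same trials.

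**Step 3: where the power goes.** The two tests differ in more than the cut. At 37 per arm:
- Noninferiority of means, one-sided 0.05: 90.5%.
- Difference in means without the margin, one-sided 0.05: 48.8%.
- Difference in means, two-sided 0.05: 36.3%.
- Chi-square, two-sided 0.05: about 13% to 28%.

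Most of the loss comes from leaving the margin out. Dichotomising takes the rest, from 36% down to 13%–28%.

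**Step 4: which way do the verdicts differ?** In the same simulation the chi-square test was positive while the two-sided t-test was not in only 3% to 7% of trials. It was positive while noninferiority failed in under 0.3%. Under these assumptions the usual disagreement is that the chi-square test misses what the comparison of means finds.

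**The case against.** The strongest defence is that the paragraph is ordered by data type. Measured data are summarised and go to analysis of variance, count data are given as rates, and ranked data go to the rank-sum test. The chi-square sentence follows the one on count data, so it was probably meant for count data, and TNSS would go to analysis of variance. That reading is plausible, and it means a comparison of means is not absent from the plan. Chi-square also has possible uses without any invented response rate: rescue use, adverse events, withdrawals and perhaps episode frequency. What stands against the defence is the wording, which says efficacy where it should say count data. Nothing else in the section says which test decides efficacy on TNSS.

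A second defence is that categorical variables are commonly defined in an analysis plan or full protocol that is not shown. That is fair, and the missing responder definition is not itself the finding. The finding is that the stated test does not fit the stated outcome and sample size.

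A reader might also infer that the sentence lets the trial claim efficacy from a response cut-off chosen after the data are seen, or that mean TNSS, a response rate and rescue use compete at full α with an inflated false-positive rate. The article does not support this. It names one primary outcome, mentions no cut-off or percentage reduction, and does not say that success on any one of several tests would count. Calling rescue use an indicator of curative effect does not make it a deciding test.

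**Conclusion.** The point holds as a conflict between the Data analysis section and the Outcome measurement and Sample size sections: the sentence on efficacy names a test that does not match the primary outcome or the sizing. If the sentence is only loosely worded count-data text, the harm is ambiguity. If it is followed literally, power falls from about 90% to about 13%–28%, and a chi-square test with 90% power would need about 203 to 629 patients per arm.

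These figures assume normal scores at the protocol's own means and SDs, 37 per arm, the one-sided 0.05 inferred from the sample size, and TNSS cut-offs of 3 to 8 that I chose. They do not show an inflated false-positive rate. Such a figure would need a rule for claiming efficacy that the article does not contain.

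**What to change.** Replace the chi-square sentence with one such as: *Count data will be compared using the χ² test.* Keep the rank-sum test for ranked data. Add that efficacy is decided only by the between-group difference in mean TNSS, tested for noninferiority against the 0.92 margin used for the sample size. List rescue use among the outcomes as supportive. If a responder rate is wanted, fix its TNSS cut-off before unblinding and label it supportive too.

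This takes a few sentences in the analysis and outcome sections and needs no extra patients, data or procedures. The price is that a responder or rescue result alone cannot be called efficacy.

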### Ethical approval

The study protocol was approved by the Ethics Committee of GDPHCM (B2016–100-01), and it will be explicitly explained to all participants that the trial involves two types of interventions, with a 2-week run-in period, 4 weeks of treatment and 12 weeks of follow-up. All participants will be given sufficient time to decide whether to sign the informed consent form. Written informed consent must be obtained from each participant before they are randomized to a group.

## Discussion

Although treatment for AR has been developed and standardized, the symptoms of some AR patients are still not well controlled with current pharmacological therapies [47, 48]. CHM, which may have an effect on AR, has gradually received increasing attention and has been adopted for the treatment of AR [8]. Syndrome differentiation or pattern identification is a specific analysis of individual body constitutions, symptoms, and signs based on TCM physiology and pathology and is performed before arriving at a diagnosis or drawing a conclusion [49]. This step must be performed before prescribing CHM formulas because accurate syndrome differentiation or pattern identification ensures accurate therapeutic effects with fewer AEs [8]. BMF is composed of modified *bu zhong yi qi tang* and *yu ping feng san*, which are typically applied to treat allergic diseases [17]. Based on previous experience with the use of BMF to treat AR, this study combines syndrome differentiation and treatment with strict RCT design principles to assess the efficacy and safety of BMF for the treatment of AR. Regarding the mechanistic study of this formulation, this study aims to determine whether BMF can modulate cytokine levels and gut microbiota.

To the best of our knowledge, this is the first double-blind double-dummy RCT aimed at determining the efficacy of BMF in treating AR patients with LSQDS. This is also the first study to investigate changes in inflammatory cytokines as well as changes in the gut microbiota with CHM-based therapy.

There are limitations to this study. The first is a lack of validated outcome measures to evaluate the body constitution of AR patients with LSQDS. In Chinese medicine theory, the body constitution of a patient is dynamic and may change after the BMF intervention. The second limitation is that the sample size calculation was based on a previous study [46] and our clinical observations; thus, the sample size of our study may have been different if more cases had been observed by a prior rigorous RCT. The last limitation is that this study explores only the mechanism by which the BMF formula treats AR and does not address the mechanism at a component level.

Despite its limitations, we believe that this study has the potential to contribute to the development of an effective intervention for AR patients with LSQDS. In the future, a multicenter RCT with a large sample of AR patients and the implementation of multidimensional comprehensive evaluations should be performed. A series of studies on BMF and its chemical components and the molecular mechanisms of actions in AR patients with LSQDS are needed and may provide consolidated evidence regarding the efficacy and safety of BMF for AR patients with LSQDS (Additional file 1).

### Trial status

The first patient in the study was enrolled on 22 December 2016. The trial has already enrolled participants: 76 AR patients have been recruited, and 40 patients had completed the trial by 7 November 2017.

## Abbreviations

16S rRNA: 16S ribosomal ribonucleic acid
AE: Adverse event
AR: Allergic rhinitis
BMF: *Bi min fang*
CHM: Chinese herbal medicine
CRF: Case report form
ELISA: Enzyme-linked immunosorbent assay
GDPHCM: Guangdong Provincial Hospital of Chinese Medicine
IFN-γ: Interferon-γ
IgE: Immunoglobulin E
IL-17: Interleukin-17
IL-4: Interleukin-4
LSQDS: Lung and spleen *qi* deficiency syndrome
RCT: Randomized controlled trial
RQLQ(S): Standard version of the Rhinoconjunctivitis Quality of Life Questionnaire
SPSS 17.0: Statistical Packages for the Social Sciences version 17.0
TCM: Traditional Chinese medicine
TGF-β1: Transforming growth factor β-1
TNSS: Total Nasal Symptom Score
VAS: Visual analog scale
